#### Secondary and Exploratory Outcomes

Data from all participants who complete baseline surveys will be included in intent-to-treat analyses [49]. Before UC crosses over to receive mPRISM, the first phase of the study can be viewed as a parallel 2-armed RCT. Given the first phase parallel group RCT design, we will first compare posttreatment efficacy outcomes between mPRISM and UC using 2-sample independent *t* tests [50]. We will explore a range of effect sizes around what is observed in this pilot trial and assume larger SEs. Exploratory efficacy will be examined using the first phase parallel RCT data with regression models [44,45]. The effect of assessment time and other unbalanced confounders will be assessed as covariates in the models [51]. Potential covariates include age, gender, and diagnosis, which have been shown to influence psychosocial outcomes [52]. Estimation will be based on restricted maximum likelihood and significance based on the Wald *t* test [53]. With regard to digital usage data, we will summarize individual digital usage metrics (eg, number of usage sessions and total duration of use) using descriptive statistics and graphical tools.

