**Methods:**

This is a parallel, 2-arm, single-site pilot RCT with a waitlist control design. The study will recruit 80 AYAs with cancer from a clinic. Eligible AYAs are aged 12 to 25 years, within 12 months of a new cancer diagnosis, receiving chemotherapy or radiation therapy, speak, read, or write in English, and are cognitively able to participate in study procedures. Recruitment by clinical research coordinators will occur remotely by phone, video, or text. Participants will be randomized to psychosocial usual care (UC) alone or UC plus mPRISM for an 8-week intervention period, and will remain unblinded to study condition. Enrolled participants will complete surveys at baseline before randomization, 8 weeks, and 3-month follow-up. Using a waitlist design, the UC arm will receive mPRISM upon completion of 3-month follow-up surveys. Those in the UC arm will complete 2 additional measurement points at immediate posttreatment and 3 months later. The primary outcomes of interest are feasibility, defined as ≥60% enrollment and ≥70% retention (ie, percentage of participants who completed the study), and “feasibility, acceptability, and appropriateness” as defined by cut-off scores ≥4/5 on 3 brief validated implementation outcome measures (feasibility of implementation measure, acceptability of intervention measure [AIM], intervention appropriateness measure [IAM]). We will apply top-box scoring for the implementation measures. Exploratory outcomes of interest include patient-reported health-related quality of life, resilience, distress, anxiety, depression, pain, and sleep. We will conduct an intention-to-treat analysis to compare the outcomes of the mPRISM arm versus the control arm with covariate-adjusted regression models. We will summarize individual digital usage metrics using descriptive statistics.

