#### Measures

Enrolled AYA participants will complete surveys at baseline before randomization, posttreatment (at 8 weeks), and 3-month follow-up (at 20 weeks). All surveys will be completed electronically by REDCap (Research Electronic Data Capture; Vanderbilt University) SMS text messaging or email survey invitation [34,35]. Survey responses will be scored based on measure scoring guidelines from the measure developers. In a waitlist design, the UC arm will receive mPRISM upon completion of the 3-month follow-up surveys to increase retention and optimize the use of the full sample size for analysis. This second wave of data collection for UC will include 2 additional measurement points at immediate posttreatment and 3 months later. Measure batteries at each timepoint take approximately 15-25 minutes to complete.

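### The first efficacy comparison is an unadjusted 8-week t test, and the covariates named for the later regression omit the baseline score, which gives up precision

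*Protocol article*

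**What the plan says.** All statements are in the Protocol article.

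- **Data collected** (Measures): "Enrolled AYA participants will complete surveys at baseline before randomization, posttreatment (at 8 weeks), and 3-month follow-up (at 20 weeks").
- **Analysis set** (Data Analysis, Secondary and Exploratory Outcomes): "Data from all participants who complete baseline surveys will be included in intent-to-treat analyses".
- **First comparison** (same section): "we will first compare posttreatment efficacy outcomes between mPRISM and UC using 2-sample independent" *t* tests.
- **Next step** (same section): "Exploratory efficacy will be examined using the first phase parallel RCT data with regression models". On covariates: "The effect of assessment time and other unbalanced confounders will be assessed as covariates in the models", and then "Potential covariates include age, gender, and diagnosis, which have been shown to influence psychosocial outcomes". On estimation: "Estimation will be based on restricted maximum likelihood and significance based on the Wald" *t* test.
- **Abstract, Methods**: "We will conduct an intention-to-treat analysis to compare the outcomes of the mPRISM arm versus the control arm with covariate-adjusted regression models".
- **Table 1**: lists regression models for patient outcomes and no *t* test.
- **Power**: the trial is not powered for efficacy. Trends are judged against a minimal clinically important difference (MCID) of half an SD.

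**The concern.** The baseline value of an outcome is usually the best single predictor of its later value, and here it is available for everyone randomized. The first comparison ignores it. The regression section does not name it either, and it describes covariates other than time as unbalanced confounders. Whether baseline enters could therefore depend on what imbalance happens to be observed.

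The *t* test also sits awkwardly beside the analysis-set sentence in the same section. A comparison of 8-week scores can use only those who have one, whereas the stated set is everyone with a baseline survey.

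What is at stake is the quality of the efficacy estimates. They are to be read against the MCID, and the Discussion and Conclusions say that they will inform the sample size and power of a larger trial. The primary feasibility, acceptability and appropriateness outcomes are not affected.

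**Working it through.** The document states no efficacy power, alpha or efficacy sample size, so there is no figure to reproduce. The calculation below only shows the size of the precision loss.

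**Inputs from the document**
- 80 participants allocated 1:1 (Trial Design), so 40 per arm.
- Retention of at least 70% counts as feasible (Primary Outcomes): 0.70 × 80 = 56, or 28 per arm if retention is equal between arms. This threshold concerns completing the study. It is used here as a proxy for 8-week response.
- MCID = 0.5 SD (Power).

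**Assumptions not in the document**
- Correlation *r* between baseline and 8-week score: 0.3 to 0.7.
- 95% confidence intervals, equivalent to two-sided alpha 0.05.

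**Formulas, in SD units, *n* per arm**
- Unadjusted half-width: *t*(0.975; 2*n* − 2) × √(2/*n*).
- Baseline-adjusted half-width: *t*(0.975; 2*n* − 3) × √(1 − *r*²) × √(2/*n*).
- Share of variance removed: *r*². Equivalent unadjusted sample per arm: *n*/(1 − *r*²).

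**Results**

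| | Variance removed | Half-width, *n* = 40 | Equivalent *n* | Half-width, *n* = 28 | Equivalent *n* |
|---|---|---|---|---|---|
| *t* test | – | 0.445 | 40 | 0.536 | 28 |
| *r* = 0.3 | 9% | 0.425 | 44.0 | 0.511 | 30.8 |
| *r* = 0.5 | 25% | 0.386 | 53.3 | 0.464 | 37.3 |
| *r* = 0.7 | 49% | 0.318 | 78.4 | 0.383 | 54.9 |

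At 28 per arm the unadjusted half-width (0.54 SD) is wider than the MCID. With adjustment it is still slightly wider at *r* = 0.3 (0.51 SD), and narrower at *r* = 0.5 (0.46 SD) and *r* = 0.7 (0.38 SD).

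**Chance imbalance at baseline.** With 40 per arm the SE of a baseline difference is √(2/40) = 0.22 SD, so the 95% range is about ±1.96 × 0.2236 = ±0.44 SD. Only about *r* times an imbalance carries into the 8-week difference. For an imbalance at the edge of that range this is 0.3 × 0.44 = 0.13 SD, 0.5 × 0.44 = 0.22 SD, or 0.7 × 0.44 = 0.31 SD.

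**Who is analysed.** If 30% lack an 8-week score, the *t* test uses 56 of 80. The other 80 − 56 = 24 belong to the stated intention-to-treat set but add nothing to that test.

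**The case against.** The strongest defence is that the *t* test is only a first step. The Abstract, Table 1 and the section itself all present regression as the efficacy analysis. A reader might infer that the plan discards baseline information altogether, and the text does not support that. The covariate list is open-ended, and an imbalanced baseline score could count as an unbalanced confounder. REML estimation with assessment time in the model also suggests repeated measures, which may carry baseline as a response. In that case baseline information would be used and participants with only a baseline survey would be kept. The article does not say which, and a statistical analysis plan that is not shown may settle it.

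A reader might also infer that the plan contradicts its own intention-to-treat set. It does not, taken as a whole: the Abstract attaches intention-to-treat to the regression. The mismatch is confined to the *t* test step, and 56 of 80 is a proxy figure, not a forecast of 8-week response.

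A third tempting reading is that chance imbalance could produce a spurious effect as large as the MCID. That overstates it. Only about *r* times the imbalance carries through, and with complete data the *t* test is unbiased under randomization, with an SE that already reflects chance imbalance.

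Finally, the gains shown compare adjustment with the *t* test alone. They do not measure a shortfall of the planned regression, whose use of baseline is unknown. Since no efficacy power is claimed, no stated figure is wrong.

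All of this stands, and it limits the point. It does not remove it: the document affirmatively puts the unadjusted test first, names covariates without the baseline score, and links covariate choice to observed imbalance.

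**Conclusion.** The point holds as a matter of efficiency and clarity. The efficacy comparison listed first ignores a pre-randomization measurement that every participant provides, and nothing in the article commits the later model to using it. Relative to the *t* test, baseline adjustment would remove 9% to 49% of the residual variance. At 28 per arm it would shorten the 95% CI half-width from 0.54 SD to 0.51–0.38 SD, against an MCID of 0.5 SD. These figures rest on an assumed correlation of 0.3 to 0.7, a 95% interval, and 70% retention, equal in both arms, standing in for 8-week response.

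The *t* test is an observed-case step and should not be read as the intention-to-treat analysis. The outcomes are exploratory, so the consequence falls on the effect estimates and intervals carried forward to the next trial and not on this trial's primary conclusions.

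**What to change.** 1. Prespecify the baseline score of the same outcome in the planned REML model, either as a covariate or as a response with arm means constrained equal at baseline. Include it regardless of observed imbalance.
2. Name that model as the main efficacy comparison in the intention-to-treat set, and report adjusted differences with 95% CIs at 8 and 20 weeks.
3. Keep any *t* test only as a descriptive observed-case summary, labelled as such and with the number analysed per arm.

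The cost is wording in the analysis plan, as no new data are needed. The Results section reports 25 participants enrolled by July 2024 and data collection expected to finish in 2027, so on those dates the change could be made well before the analysis. If the full analysis plan already fixes the role of baseline, only the order and labelling of the *t* test need attention.

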## Methods

### Study Aims

The primary aim of this study is to evaluate the feasibility and acceptability of a self-guided mHealth resilience intervention (mPRISM) for AYAs with cancer. mPRISM content is based on stress and coping theory, resilience theory, and evidence-based psychosocial interventions. We hypothesize that mPRISM will be feasible as measured by ≥60% enrollment and ≥70% retention of participants to complete the study; and feasible, acceptable, and appropriate as measured by 3 brief well-established implementation measures (feasibility of intervention measure [FIM], acceptability of intervention measure [AIM], and intervention appropriateness measure [IAM] scores ≥4/5) [31]. Exploratory aims are to (1) examine preliminary efficacy assessed by validated patient-reported outcome measures at posttreatment and 3-month follow-up and (2) summarize digital usage metrics and engagement patterns under naturalistic conditions to inform future study design and to prepare participant instructions on how to use the app.

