### Data Analysis

#### Power

The role of rigorous pilot studies such as this study is designed to determine feasibility [44,45]. Although not powered for efficacy, we will examine preliminary efficacy data for meaningful trends in terms of clinical significance with minimal clinically important difference (MCID) defined as half the SD for outcomes [46].

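### The efficacy regression selects covariates by observed imbalance, does not name the baseline score, and states no 3-month arm contrast although the aim asks for one

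*Protocol article*

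**What the plan says.** The Study Aims section gives the first exploratory aim as to "examine preliminary efficacy assessed by validated patient-reported outcome measures at posttreatment and 3-month follow-up". The Measures section has participants "complete surveys at baseline before randomization, posttreatment (at 8 weeks), and 3-month follow-up (at 20 weeks"), so the phase before the control arm receives the app has one pre-randomization wave and two follow-up waves.

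The Secondary and Exploratory Outcomes part of Data Analysis describes two steps:

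- An unadjusted comparison at one time point: "we will first compare posttreatment efficacy outcomes between mPRISM and UC using 2-sample independent" *t* tests.
- A regression step: "Exploratory efficacy will be examined using the first phase parallel RCT data with regression models". On the model terms it says "The effect of assessment time and other unbalanced confounders will be assessed as covariates in the models", and then "Potential covariates include age, gender, and diagnosis, which have been shown to influence psychosocial outcomes". On fitting it says "Estimation will be based on restricted maximum likelihood and significance based on the Wald" *t* test.

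No arm-by-time term and no 3-month arm contrast is mentioned. The baseline value of the outcome is not among the named covariates, and the text does not say whether baseline enters as an outcome wave or as an adjustment variable. The Power section reads the efficacy estimates against a "minimal clinically important difference (MCID) defined as half the SD for outcomes". The Discussion says that the patient-reported outcomes will inform the sample size of later powered trials.

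**The concern.** There are two issues, and neither causes the other.

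**Covariate selection.** Under randomization, a difference between arms in age, gender or diagnosis arises by chance. How large it happens to be says nothing about how strongly the variable predicts the outcome, and it is prognostic strength that makes adjustment worthwhile. A rule based on observed imbalance lets chance pick the model, after arm-level data are visible. The covariate likely to be the strongest predictor, the participant's own baseline score, is not named. It costs nothing to collect: randomization follows completion of the baseline surveys, and the intention-to-treat set is everyone who completed them.

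**Time-specific effects.** The aim names two time points. REML estimation with assessment time as a covariate suggests a pooled repeated-measures model. With arm and time as main effects only, such a model returns one arm coefficient, which is neither the 8-week nor the 3-month effect unless the two are equal.

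What is at stake is the estimate compared with the half-SD benchmark and carried into planning the next trial.

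**Working it through.** The protocol gives no figure for this regression, so there is none to reproduce. The checks below take 80 participants at 1:1 (40 per arm) and the 0.5 SD benchmark from the protocol. Within-person correlation, the definition of unbalanced and the pattern of effects over time are assumptions.

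**1. How often would a covariate look unbalanced by chance?**
For a covariate with SD 1, the standard error of the difference between arms is √(2/40) = 0.2236. The chance that the absolute difference exceeds 0.2 is 2 × [1 − Φ(0.2/0.2236)] = 0.371. For three independent covariates the chance of at least one is 1 − (1 − 0.371)³ = 0.75. The protocol does not define unbalanced, so the range over common definitions is:

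| Definition | One covariate | At least one of three |
|---|---|---|
| *p* < 0.05 | 0.05 | 0.14 |
| *p* < 0.10 | 0.10 | 0.27 |
| Standardized difference > 0.2 | 0.37 | 0.75 |
| Standardized difference > 0.1 | 0.65 | 0.96 |

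The spread from 0.14 to 0.96 shows how far an undefined rule leaves the model open. The normal approximation is rough for gender and diagnosis, which are categorical.

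**2. What does the baseline score add?**
For one follow-up wave with complete data, the standard error of the arm contrast is √(2/40) = 0.224 SD unadjusted and √(2(1 − ρ²)/40) adjusted for baseline. The adjusted value is 0.213, 0.194 and 0.160 SD at ρ = 0.3, 0.5 and 0.7. For a true 0.5 SD effect at a two-sided 5% level, power is about 0.61 for the unadjusted *t* test and 0.73 for the adjusted contrast at ρ = 0.5.

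**3. What does a main-effects model estimate?**
Under a random intercept (equal correlation between waves) and complete data, the generalized least squares arm coefficient is the simple mean of the wave-specific arm differences, whatever the correlation.

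- Two follow-up waves, true effects 0.5 and 0.5: (0.5 + 0.5)/2 = 0.50. No dilution.
- Two follow-up waves, true effects 0.5 and 0.2: (0.5 + 0.2)/2 = 0.35, which is neither effect.
- Baseline also an outcome wave, true effects 0, 0.5 and 0.5: (0 + 0.5 + 0.5)/3 = 0.33.

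In the last case dropout lowers the figure further, because baseline then carries more weight. If 30% were lost after baseline completely at random (the protocol's 70% retention threshold), the coefficient is 0.27, 0.26 and 0.25 at ρ = 0.3, 0.5 and 0.7.

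**4. Consequence for the next trial, in that last case only.**
Required sample size varies with 1/effect², so planning on 0.33 instead of 0.50 SD multiplies it by (0.50/0.333)² = 2.25.

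**5. Which of the two effects does a stated analysis deliver?**
At 8 weeks the *t* test gives an unadjusted contrast. At 20 weeks no contrast, adjusted or unadjusted, is stated. No adjusted contrast specific to either time point is stated.

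**The case against.** The strongest reply is that the article prints no model formula. It speaks of regression models in the plural, and calling time a covariate does not exclude an interaction, separate models per time point or baseline adjustment. A condensed article may leave such details to a full protocol or analysis plan. This stands to a large extent. A reader might infer that the planned model will certainly produce one diluted arm effect; the text does not support that. Dilution needs baseline as an outcome wave and no arm-by-time term, and neither is stated. The aim names only the two follow-ups as efficacy time points, which favours the reading without dilution.

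A reader might also infer that neither effect in the aim is estimated. That is wrong for 8 weeks, where the *t* test gives an undiluted if unadjusted contrast.

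Other points for the plan are fair. Surveys are completed remotely, so assessment time could mean actual completion time, which can vary between participants, rather than a wave indicator. The named candidates are few and are justified by their relation to psychosocial outcomes. The plan also intends to explore a range of effect sizes, efficacy is explicitly unpowered, and no decision rule rests on this coefficient.

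These points do not remove the imbalance criterion, which is stated text rather than missing detail. Nor do they supply a 3-month contrast or name the baseline score. The prognostic justification given for age, gender and diagnosis is itself a reason to fix them in advance.

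**Conclusion.** The point holds, with low to moderate severity.

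- **Covariates:** the stated rule makes adjustment depend on chance. The probability that at least one of three covariates is flagged is about 75% at a standardized difference of 0.2, assuming 40 per arm and independent covariates, and 14% to 96% across the definitions shown. The baseline score is not named. Adjusting for it would cut the standard error of a single-wave contrast from 0.224 to between 0.213 and 0.160 SD for correlations of 0.3 to 0.7.
- **Time:** read literally, the regression yields one averaged arm coefficient, and the 3-month effect in the aim has no stated contrast. The 8-week effect has an unadjusted one.
- **Dilution:** the fall from 0.50 to about 0.33 SD is conditional. It needs baseline modelled as an outcome wave, no arm-by-time term and complete data, with a constant true effect at both follow-ups. It should be treated as a risk that the wording leaves open, not as a property of the plan.

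The exploratory status keeps the severity down. It does not reduce it to nothing, because the estimates are set against a half-SD benchmark and are meant to inform a later trial's sample size.

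**What to change.** Replace the sentence on unbalanced confounders with a stated model for the first-phase data: outcomes at 8 and 20 weeks; terms for arm, categorical time and arm-by-time; the baseline score of the same measure; and a prespecified set of age, gender and diagnosis group, kept whatever imbalance is observed. State that baseline is an adjustment variable and not an outcome wave. Report the adjusted arm contrast with a confidence interval at each of the two time points. The 8-week *t* test can stay as an unadjusted companion.

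The cost is a change of wording and a few model degrees of freedom: one for the interaction, one for the baseline score and those for the fixed covariates. Diagnosis should be grouped coarsely, given 80 participants. No extra data are needed. The article expects data collection to finish in 2027, which leaves time to settle this before arm-level outcomes are examined.

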### Ethical Considerations

All procedures are approved by the Seattle Children’s Hospital Institutional Review Board (STUDY00004006). The trial is registered at ClinicalTrials.gov (NCT05842902). All participants will provide informed consent (18-25 years old) or assent with parental consent (12-17 years old). Study participation is completely voluntary and participants are allowed to opt out of the study at any time. Privacy and confidentiality protections will be in accordance with institutional ethical guidelines. Study data are collected on secure, internal, HIPAA-compliant REDCap servers only accessible to the study team [34,35]. The collection of identifiable information is limited to that required to contact participants for study procedures and to report on sample demographics. Participants consented to use of data for study publications and no individually identifiable information will be reported in study publications. Participants will be compensated US $25 in electronic gift cards for completing each survey.

